### **5.2 Exclusion Criteria**

1. Patients with any contraindications listed on the package insert for magnesium oxide/naldemedine or with a history of hypersensitivity to any ingredients of these medicine
2. Patients with a serious gastrointestinal structural anomaly (e.g: mechanical ileus), a disease that influences intestinal transit (e.g: paralytic ileus, peritoneal dissemination, peritoneal cancer, uncontrolled hyper/hypothyroidism), irritable bowel syndrome (IBS), inflammatory bowel disease (IBD, e.g: ulcerative colitis, crohn's disease), active diverticular disease, pelvic disorders that cause constipation (e.g: uterine prolapse, rectal prolapse, myoma of the uterus that influences defecation). Or, patients decided by the doctor to have serious influence on gastrointestinal function (e.g: difficulty with oral intake), even if the disease written above are cured
3. Breastfeeding women or women with possible pregnancy
4. Patients who had undergone a surgery or a treatment that influences gastrointestinal function (e.g: nerve block) 28days within the enrolment day, or patients planning to take them during the observation period

## **6. Patients Registration and Enrollment procedures**

### **6.1 Study registration**

This study will be registered in the UMIN Clinical Trials Registry (UMIN-CTR) [<http://www.umin.ac.jp/ctr/index-j.htm>] and will be available to the public. The study will be registered prior to its implementation.

## 6.2 Registration of other study sites

Not applicable.

## 6.3 Enrollment Procedures

The Investigator or co-investigators will obtain written informed consent from a potential patient. After obtaining patients' consent, the investigator or others will make sure that the patient meets all the inclusion criteria and does not meet any exclusion criteria and then enroll the patients. The investigator or others will fill out the registration form and notify the data center. The data center will check the patient's eligibility and when eligible, the principal investigator or co-investigator will be notified of the patient ID number and drug name by fax by the data center.

Data center:

Department of Gastroenterology and Hepatology, Yokohama City University

Hospital

[contact]

[contact]

reception hours: 10:00 a.m. to 5:00 p.m. weekdays

## 6.4 Method of randomization

Eligible patients will be randomly assigned (1:1) to receive 500 mg magnesium oxide thrice daily, or 0.2 mg naldemedine once daily at the central registration center. Randomization will be carried out after the patient has signed the informed consent form. To avoid a large bias, we will stratify age ( $<65$ ,  $\geq 65$ ) and gender (male, female) using computer-generated administered procedure, in permuted-block method.

## 6.5 Blinding of patients and physicians

Masking of patients and physicians is not applicable because this is an open label study, but outcome evaluator will be masked to treatment assignment.

# 7. Study treatment

## 7.1 Name of study drugs

- Magnesium oxide group:  
magnesium oxide 500mg (1 tablet), thrice daily after each meal  
orally administer for 12 weeks
- Naldemedine group:  
naldemedine 0.2 mg/day (1 tablet) once daily after breakfast  
orally administer for 12 weeks

## 7.2 Criteria for dose reduction and drug withdrawal

When side effects such as diarrhea occur and the physician judges continuing the treatment would be to the detriment of the patient, the dosage will be reduced, or the drug will be withdrawn.

## 7.3 Criteria for discontinuation

If the patient meets any of the following criteria, the investigator will discontinue the protocol treatment. The "date of discontinuation" is the date when the physician in charge decides to discontinue, not the date when the event that is the reason for discontinuation occurs. Discontinuation cases in (1) through (3) will continue to be observed as long as possible.

- (1) When a grade 3 or more severe AE according to the NCI-CACTE version 4.0 occurs
- (2) When oral compliance with the study medication is less than 80%
- (3) When the patient requests discontinuation of the study
- (4) When continuous medical examination becomes challenging due to patient's relocation, change in hospital or busy schedule, etc.
- (5) When the patient turns out to be ineligible for the trial after enrollment
- (6) When the physician in charge of the study determines that the continuation of the study treatment is not possible for any other reasons

## 7.4 Concomitant Therapy

### 7.4.1 Prohibited Concomitant Therapy

- (1) Regular use of laxatives other than protocol drugs
- (2) Investigational or test drugs other than protocol drugs

### 7.4.2 Continuous Prior Treatment and Concomitant Therapy

Drugs used more than 4 weeks prior to this study can be used concomitantly if the dosage

and administration have not been changed at least 4 weeks prior to the start of the study. Diet, exercise therapies and symptomatic treatment for complications and adverse events can also be performed concomitantly. Stimulant laxatives are allowed to be used as a rescue medication for constipation.

7.5 After the study

Laxatives can be continued or changed according to the patient's condition.

**8. Summary of Known and Potential Risks and Benefits in Patients**

8.1 Potential Risks and Benefits in Patients

Taking the study drug may cause occasional or psychological burden. In addition, the study drug may cause side effects due to drug administration. Side effects and adverse events will be appropriately evaluated by medical examination and blood tests at regular visits during the study period. In addition, investigators will make it known to all participants that they can consult with them at any time to promptly respond to any symptoms of side effects that may arise, even outside of the visits specified in the protocol. There is a reasonable possibility that the study drug will provide benefits such as improvement of clinical symptoms and quality of life that have been caused by OIC. There will be no financial benefit from participation in the study.

8.2 Definitions of Adverse Events

Any unfavorable symptoms or signs (including abnormal laboratory values) occurring within 4 weeks of protocol completion will be reported as an adverse event (AE). AEs may or may not be causally related to the protocol treatment.

8.3 Assessment of Adverse Events

The degree of AE will be assessed according to the Common Terminology Criteria for Adverse Events v4.0 as follows.

|                    |                                                          |
|--------------------|----------------------------------------------------------|
|                    | Asymptomatic or mild symptoms; clinical or               |
| Grade 1 (mild)     | diagnostic observations only; intervention not indicated |
|                    | Minimal, local or non-invasive intervention              |
| Grade 2 (moderate) | indicated; limiting age-appropriate instrumental ADL     |

|                            |                                                                                                                                                             |
|----------------------------|-------------------------------------------------------------------------------------------------------------------------------------------------------------|
| Grade 3 (severe)           | Medically significant but not immediately life-threatening; hospitalization or prolongation of hospitalization indicated; disabling; limiting self-care ADL |
| Grade 4 (life-threatening) | Life-threatening consequences: urgent intervention indicated                                                                                                |
| Grade 5 (death)            | Death related to AE                                                                                                                                         |

---

Causal relationship with protocol treatment is classified into three categories as follows.  
Associated: Causal relationship with protocol treatment is reasonable. Not due to exacerbation of the primary disease, complications, or other treatments.

Can be associated: Causal relationship with protocol treatment is unclear. Can be explained by exacerbation of the primary disease, complications or other treatments, etc.

Not associated: No causal relationship with protocol treatment. Can be clearly explained by exacerbation of the primary disease, complications or other treatments, etc.

Serious AEs are defined as follows.

- (1) Causes death
- (2) Life-threatening
- (3) Requires hospitalization or prolonged hospitalization/recuperation
- (4) Causes permanent or significant disability or malfunction
- (5) Causes congenital anomaly or congenital defect
- (6) Other medically important conditions (serious events that require prevention not to reach 1-4 conditions)

#### 8.4 Expected Adverse Events

The efficacy and safety of the study drugs for patients with OIC or constipation have been confirmed in clinical trials, and the inclusion criteria for suitable patients for administration is established. The study will be conducted with adequate safety monitoring. This is an open-label, randomized controlled trial comparing two groups of study drugs, and there is not enough evidence to show that one is superior to the other. In this study, all medical care during the study period, including study treatment, will be provided as usual medical practice. The medical cost will be covered by insurance. The frequency of visits and examinations in this study will

be the same as in the regular medical practice.

Side effects of the study drugs are as follows.

Magnesium oxide: abdominal pain (1.1%), mild diarrhea (1.1%), mild increase in plasma magnesium levels (9.5%)

Naldemedine: diarrhea (21.9%), abdominal pain (2.2%)

## 8.5 Response to Serious Adverse Events (SAE)

### 8.5.1 Emergency Reporting of Serious Adverse Events

When a SAE occurs, the co-investigator will immediately report it to the principal investigator. The principal investigator will immediately report the details to the Hospital Director. The hospital director will obtain opinions from the Ethical Review Committee and take necessary measures in accordance with the procedures of the study institution. When an unpredictable SAE which relationship between the study drug cannot be ruled out occurs, the hospital director will promptly report the event to the Minister of Health, Labor and Welfare and notify the principal investigator or the study site.

### 8.5.2 General Reporting of Adverse Events

When an AE occurs, the principal investigator or co-investigator will write a Case Report Form and report it to the principal investigator (or study site).

## 9. Study schedule

### 9.1 Planned Duration of Patient Participation

Protocol treatment period: 12 weeks

Study period: From March 22, 2018 to March 31, 2023

Recruitment period: From March 22, 2018 to March 31, 2021

### 9.2 Observation, Test and Investigation Items

#### 9.2.1 Patient's background

The patient's background will be examined in the baseline period before enrollment. Data from within 1 month prior to enrollment will be used.

- Height, weight, BMI, age, and sex
- Location of cancer, past history, complications, surgical history
- Current medication and dosage
- Allergy

### 9.2.2 Clinical findings

Patient's QOL and clinical symptoms will be investigated using the PAC-QOL/PAC-SYM/CSS questionnaires. The presence of constipation will be assessed using the Rome IV criteria and stool shape will be assessed using the Bristol Stool Form Scale. Patients will be randomized after study enrollment and will be seen at 2 weeks ( $\pm 7$  days), 12 weeks ( $\pm 14$  days) and at the time of discontinuation ( $\sim +2$  days) and the PAC-QOL/PAC-SYM/CSS/Rome IV/ Bristol Stool Form Scale/SMBs questionnaires will be performed at the visits.

### 9.2.3 Compliance with treatment/ assessment of QOL

Quality of life will be assessed by filling in the questionnaire at 2 weeks after the start of the study and at the end of the study (at 2 and 12 weeks). Compliance with the study medication will be assessed by asking the patients to return the unused tablets at the last visit (at 12 weeks).

## 9.3 Observation, Test and Investigation schedule

|                           | Before enrolment                   | treatment period |   |   |   |    |    |
|---------------------------|------------------------------------|------------------|---|---|---|----|----|
| Week                      | 4weeks before enrolment (baseline) | 2                | 4 | 6 | 8 | 10 | 12 |
| Patients' background      | ⊙                                  |                  |   |   |   |    |    |
| Physical examination      | ⊙                                  | ⊙                | ○ | ○ | ○ | ○  | ⊙  |
| Symptoms (adverse events) | ⊙                                  | ⊙                | ○ | ○ | ○ | ○  | ⊙  |
| JPAC-QOL                  | ⊙                                  | ⊙                |   |   |   |    | ⊙  |
| PAC-SYM                   | ⊙                                  | ⊙                |   |   |   |    | ⊙  |
| CSS                       | ⊙                                  | ⊙                |   |   |   |    | ⊙  |
| RomeIV                    | ⊙                                  | ⊙                |   |   |   |    | ⊙  |

|       |   |   |  |  |  |  |   |
|-------|---|---|--|--|--|--|---|
| BSFS  | ◎ | ◎ |  |  |  |  | ◎ |
| SBMs  | ◎ | ◎ |  |  |  |  | ◎ |
| SF-36 | ◎ | ◎ |  |  |  |  | ◎ |

◎ To be performed

○ When necessary

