#### 0.5 Study method

The study consists of a screening period for 4 weeks and a treatment period for 12 weeks. Cancer patients scheduled to commence opioid therapy will be randomly

allocated into magnesium oxide (500mg (1 tablet), thrice daily after each meal) or naldemedine (0.2 mg/day (1 tablet), once daily after breakfast) groups and will orally administer each study drug for 12 weeks during the treatment period.

The primary endpoint will be the change in the Japanese version of The Patient Assessment of Constipation Quality of Life (JPAC-QOL) from baseline at 2 weeks. The Patient Assessment of Constipation Symptoms (PAC-SYM), the Constipation Scoring System (CSS), the Bristol Stool Form Scale will also be examined. The presence of constipation will be assessed before and after drug administration using the Rome IV criteria.

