### **5.1 Inclusion Criteria**

1. Patients who received adequate explanation about this study and provided written informed consent
2. Patients who are  $\geq 20$  and  $< 85$  years of age at the time of informed consent
3. Patients who have not started opioid therapy
4. Patients who are scheduled to commence opioid therapy for cancer pain
5. Patients capable of oral intake
6. Patients capable of reporting the patient reported outcomes (PRO)
7. Patients who are prospectively to stay in the stable pathological condition during the observation period

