## 10. Study endpoints

### 10.1 Primary Endpoint

The change in JPAC-QOL from baseline at 2 weeks

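### The primary 2-week change in JPAC-QOL has no baseline fixed at randomisation: as scheduled it spans 5 to 7 weeks, or 1 to 7 weeks if the baseline column is a window

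*Protocol*

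**What the plan says.** Protocol section 10.1 defines the primary endpoint: "The change in JPAC-QOL from baseline at 2 weeks".

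The schedule in section 9.3 has a single pre-treatment column, "4weeks before enrolment (baseline)". JPAC-QOL and every other questionnaire are marked there, and next at week 2 of the treatment period. No column exists for enrolment, randomisation or first dose.

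Three other sections bear on how that column should be read:

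- Section 0.5: "The study consists of a screening period for 4 weeks and a treatment period for 12 weeks".
- Section 9.2.1, on background items such as height, cancer site and medication: "Data from within 1 month prior to enrollment will be used". JPAC-QOL is not in that list.
- Section 9.2.2: "Patients will be randomized after study enrollment and will be seen at 2 weeks", with a tolerance of ±7 days.

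Section 9.2.3 places the first on-treatment quality-of-life form "at 2 weeks after the start of the study" and does not say which event starts the study. On opioids, section 5.1 requires patients who have not yet begun them and adds: "Patients who are scheduled to commence opioid therapy for cancer pain". No section dates the first opioid dose relative to enrolment, randomisation, first study dose or the week-2 visit.

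**The concern.** A change score is only as well defined as its two end points. Here the later one may move by half the nominal interval either way, and the earlier one sits up to four weeks before the patient enters the trial. The patients have cancer and pain about to need opioids, so their condition can be expected to move over such a period. Whatever changes between the baseline form and the first study dose is counted in the primary endpoint although neither drug can have caused it.

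Two things are at stake. The first is precision. Section 11.2 analyses the change itself, by one-way analysis of variance or t-test, so a baseline that correlates less well with week 2 goes straight into the standard deviation of the outcome. The second is meaning. A reader of the result will take it as a 2-week effect, whereas by the schedule the interval may be seven weeks.

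The missing opioid date is a related gap. The trial is about preventing constipation caused by opioids, and a patient seen early whose opioid began late could have little or no exposure to that cause at the primary assessment.

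A later analysis plan cannot repair this, because it cannot supply a day-0 questionnaire that was never collected.

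**Working it through.** **The plan's only computed figure.** Section 11.1 assumes a difference of 1.19 − 0.76 = 0.43, a standard deviation of 0.76, two-sided 5% and 90% power, and states 51 per group. The normal formula gives 2 × [0.76 × (1.960 + 1.282) / 0.43]² = 65.6, so 66 per group; the noncentral t gives 67. The stated 51 does not reproduce: it gives 80.8% power (81.5% by the normal approximation). That is a separate matter and the timing point does not rest on it, but it is why the power illustration below starts from 81% and not 90%.

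**Length of the primary interval.** Inputs: baseline *b* days before enrolment (sections 9.3 and 0.5) and a week-2 visit at 14 ± 7 days, that is day 7 to day 21 (section 9.2.2). Enrolment, randomisation, first dose and start of study are treated as one day 0, because the protocol does not separate them. Span = *b* + (14 ± 7).

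| Reading of the baseline column | *b* (days) | Shortest | Longest |
|---|---|---|---|
| Fixed point, 4 weeks before enrolment | 28 | 28 + 7 = 35 d (5 wk) | 28 + 21 = 49 d (7 wk) |
| Window over the 4-week screening period | 0 to 28 | 0 + 7 = 7 d (1 wk) | 28 + 21 = 49 d (7 wk) |
| One-month look-back of section 9.2.1, if applied to JPAC-QOL (assumption) | 0 to 31 | 7 d (1 wk) | 31 + 21 = 52 d (7.4 wk) |

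Under the first reading no patient can have a 2-week change. Under the second some can, but nothing requires it. An upper end of at least seven weeks is common to all three; the one-week lower end needs a window.

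**Opioid exposure at the week-2 visit.** The lags are assumptions, since the protocol gives none.

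| Opioid starts | Exposure at the visit |
|---|---|
| On day 0 | 7 to 21 days |
| 7 days later | 0 to 14 days |
| 14 days later | 0 to 7 days |

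This does not enter the span above. It is a second source of heterogeneity.

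**Illustration of the effect on power.** With equal variances at the two visits, SD(change) = σ√[2(1 − ρ)], so moving from ρ = 0.6 to ρ′ multiplies it by √[(1 − ρ′)/(1 − 0.6)]. Assumed: 0.76 corresponds to ρ = 0.6. The difference is held at 0.43, with 51 per group, two-sided 5% and the noncentral t.

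| ρ′ (assumed) | SD multiplier | SD of change | Power |
|---|---|---|---|
| 0.60 | 1.00 | 0.76 | 81% |
| 0.55 | √(0.45/0.40) = 1.06 | 0.81 | 76% |
| 0.50 | √(0.50/0.40) = 1.12 | 0.85 | 72% |
| 0.40 | √(0.60/0.40) = 1.22 | 0.93 | 64% |

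**After the fix.** With the baseline on day 0 and the ±7-day tolerance kept, the span is 7 to 21 days. If a tolerance of ±3 days were also chosen, it would be 11 to 17 days.

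**The case against.** The strongest reply is that the column is a window. Its group heading refers to the time before enrolment, section 0.5 speaks of a 4-week screening period, and section 9.2.1 uses similar language for background data. A baseline at or near enrolment is then allowed, and 49 days is only the permitted extreme. This is the more natural reading, and it means one cannot say that every baseline is four weeks old by design. What remains is that the protocol does not say so and does not require a form near randomisation.

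It can also be said that the schedule puts week 2 under the treatment period, which points to the start of study drug as the origin. That is fair, but section 9.2.3 uses a different, undefined origin. The flowchart in section 0.1 was not available to this review and may show day 0 or the order of opioid start.

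A reader might infer four stronger things that the document does not support:

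- *A bias between the arms.* Both arms share the same baseline rule and visit window under 1:1 randomisation, so drift before treatment should be similar on average and cancel from the expected difference. Visit timing could differ by arm in an open-label trial, but nothing shows that it would.
- *A known loss of power.* Neither correlation is in the protocol. The 0.76 is stated beside a retrospective analysis of 10 patients whose assessment times are not given, so it cannot be tied to any particular baseline timing.
- *Weakened baseline adjustment.* Section 11.2 names no baseline covariate for the primary analysis.
- *That week 2 should be counted from the first opioid dose.* This would anchor the endpoint to an event after randomisation that may be delayed or never happen. Some patients would have no defined primary time point, and time on study drug would vary.

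**Conclusion.** The point holds as a defect of definition and precision. The nominal 14-day primary change spans 35 to 49 days if the baseline column is a fixed time point and 7 to 49 days if it is a window over screening. The protocol does not settle which, and it does not define the day from which week 2 is counted. These ranges rest only on sections 9.3, 0.5 and 9.2.2 and on treating enrolment and start of treatment as the same day; any gap between them would lengthen the span.

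The expected consequence is a noisier outcome and an unclear estimand in both arms, with the treatment contrast diluted where exposure at the visit is short. The illustrated power of 76% to 64%, against 81%, shows the direction and a plausible order of size under assumed correlations. It is not an estimate for this trial. The correction is worth making because it is cheap and concerns the only primary endpoint.

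**What to change.** 1. In section 9.3, schedule JPAC-QOL and the other baseline questionnaires on the day of enrolment and randomisation, before the allocation is disclosed and before the first study-drug dose, and state that this value is the baseline. Section 6.3 has the data center fax the drug name after registration, so the forms should be complete before the registration form is sent.
2. Define day 0 as randomisation or first study dose, and count week 2 from it in sections 9.2.2 and 9.2.3. If first dose is chosen, record both dates so that any gap is visible.
3. Record the date of the first opioid dose, report opioid exposure at the week-2 visit by arm, and add a sensitivity analysis that takes it into account. Keep the primary endpoint anchored to day 0.
4. Optionally, narrow the week-2 window for the questionnaire. How far is a matter of feasibility, and the first two changes do not depend on it.

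The cost is an amendment to the schedule and its wording, one set of questionnaires to be completed on the randomisation day, and one added date on the case report form. Treatment is not affected.

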#### 10.2.2 Safety endpoint

Incidence of adverse events that occurred from the first day to 28 days after treatment

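### Between weeks 2 and 12 adverse events are asked about only at the discretion of staff who know the arm, so the chi-squared comparison of adverse-event frequency is open to differential ascertainment of mild or transient events

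*Protocol*

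**What the plan says.** Protocol 9.3 gives the adverse-event row and the physical-examination row the compulsory symbol at baseline, week 2 and week 12. At weeks 4, 6, 8 and 10 both rows carry the open circle, which the key explains as "When necessary". Nothing in the protocol says what makes a check necessary.

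Section 9.2.2 names the post-randomization visits: "Patients will be randomized after study enrollment and will be seen at 2 weeks", then at week 12 and at discontinuation. What it lists for those visits is the bowel and quality-of-life questionnaires, not adverse-event questioning.

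Section 8.1 states: "Side effects and adverse events will be appropriately evaluated by medical examination and blood tests at regular visits during the study period". It adds that participants may consult the investigators at any time, "even outside of the visits specified in the protocol".

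On masking, section 6.5 says: "Masking of patients and physicians is not applicable because this is an open label study". The same sentence goes on to say that an outcome evaluator will be masked, without saying whether that role covers adverse events. Under 8.5.2 the principal investigator or a co-investigator writes the adverse-event report.

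The safety endpoint in 10.2.2 is "Incidence of adverse events that occurred from the first day to 28 days after treatment". Section 11.2 assigns the chi-squared test to adverse-event frequency.

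**The concern.** A comparison of adverse-event frequency between arms is fair when both arms are asked in the same way at the same times. Here that holds at weeks 2 and 12. Between them, whether a patient is asked depends on a physician who knows the drug and has no written trigger. The expected rates in section 8.4 differ widely (diarrhea 21.9% on naldemedine, mild diarrhea 1.1% on magnesium oxide), which gives a reason to ask more often in one arm.

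At stake is the safety comparison, not the primary endpoint. A short bout of diarrhea or abdominal pain at week 6 could be noted in one arm and go unrecorded in the other. The analysis cannot recover events that were never asked about, and nothing in the protocol marks which events came from scheduled and which from discretionary contacts.

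**Working it through.** **Inputs from the protocol**
- Compulsory on-treatment checks: weeks 2 and 12 (9.3). Nominal gap: 12 − 2 = 10 weeks. With the 9.2.2 windows (±7 and ±14 days) at opposite extremes, the gap is 14 − 1 = 13 weeks.
- Planned size: 60 per arm (0.4).
- Test: chi-squared on adverse-event frequency (11.2), read here as a comparison between arms, two-sided 5%, without continuity correction.
- The protocol gives no error rate, power or capture figure for the adverse-event comparison, so there is no planned figure to reproduce.

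**Assumptions, not in the documents**
- True incidence *p* is the same in both arms.
- A fraction *c*₁ of patients with the event is recorded as such in one arm and *c*₂ in the other. The range shown runs from equal capture to 100% against 50%.

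**Formula**
The recorded counts are X₁ ~ Bin(60, *p·c*₁) and X₂ ~ Bin(60, *p·c*₂). With p̄ = (x₁ + x₂)/120, the statistic is (x₁/60 − x₂/60)² / [p̄(1 − p̄)·2/60], and the test rejects above 3.84. The rejection probability is summed exactly over all pairs (x₁, x₂).

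**Results at *p* = 20%**

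| Capture | Recorded incidence | Spurious difference | Rejection probability |
|---|---|---|---|
| 100% vs 100% | 20% vs 20% | 0 points | 5.0% |
| 60% vs 60% | 12% vs 12% | 0 points | 4.9% |
| 100% vs 90% | 20% vs 18% | 2 points | 5.8% |
| 100% vs 80% | 20% vs 16% | 4 points | 8.5% |
| 100% vs 60% | 20% vs 12% | 8 points | 21.4% |
| 100% vs 50% | 20% vs 10% | 10 points | 32.6% |

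**Sensitivity to incidence**, for 100% against 80%, 60% and 50%:
- *p* = 21.9%: 9.2%, 23.7% and 35.9%.
- *p* = 40%: 14.9%, 47.6% and 68.4%.

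**What this shows**
1. Missing events equally in both arms does not inflate the test (4.9% at 60% capture in each). Only unequal capture does, so the remedy is symmetry rather than more visits.
2. *c* is capture over the whole study, including events found at the compulsory checks. If half of events could be found only by discretionary questioning and 60% of those were found, overall capture would be 0.5 + 0.5 × 0.6 = 80%. At *p* = 20% that is the 8.5% row. The lower rows need a larger exposed share or a stronger asymmetry.

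**The case against.** The strongest case against is that little is left exposed. Every patient still on study is checked at weeks 2 and 12. The endpoint is incidence, so a week-6 event still counts if it is reported at week 12. Patients in both arms are told they may consult at any time. Visits follow usual practice in a proof-of-concept phase II trial, and adverse events are a secondary matter.

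Most of this stands, and it confines the point to mild or transient events that are not recalled later. It does not remove the point. Spontaneous reports come from patients who also know their drug, and recall at week 12 covers a nominal 10 weeks.

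Three stronger readings are tempting, and the documents do not support them.
- *That 9.3 contradicts 8.1 over visits.* Section 8.1 gives no weeks and sets regular visits against contacts outside those the protocol specifies. Its regular visits can be read as weeks 2 and 12, where the check is compulsory. The clearer mismatch is that 8.1 promises blood tests and 9.3 has no blood-test row.
- *That the whole comparison turns on which patients are questioned.* The compulsory checks rule that out.
- *That grade 3 events would escape the discontinuation rule in 7.3.* By the definitions in 8.3 such events are medically significant, and they are unlikely to wait for a routine question. Section 8.1 provides for unscheduled consultation.

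On masking, it would be incomplete to cite 6.5 only for its unmasked patients and physicians, because it also names a masked evaluator. That evaluator's role for adverse events is undefined. Even if it covered grading, it would not govern whether an unmasked physician asks at week 6.

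**Conclusion.** The point holds in a limited form. Adverse-event enquiry between weeks 2 and 12 is discretionary and has no criterion. The investigators who record the events know the arm and expect very different diarrhea rates. The chi-squared comparison is therefore open to differential ascertainment of mild or transient events between those visits.

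The size cannot be derived, because the documents give no capture rates. At an assumed 20% true incidence in both arms with 60 per arm, the false-positive rate runs from about 6% to 33% as one arm's relative capture falls from 90% to 50%, against 5% with equal capture. These figures show sensitivity and are not a forecast. That investigators do the interim questioning is an inference from 6.5 and 8.5.2, since 9.3 does not say who does it. The primary endpoint is not affected.

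**What to change.** - **9.3 and 9.2.2:** require one identical symptom checklist, covering the whole interval since the last scheduled contact, for every patient in both arms at week 2, week 12 and the discontinuation visit. Where patients attend at weeks 4–10 as routine care, make the same symptom check compulsory for both arms.
- **10.2.2 and 11.2:** keep all adverse events in the main safety endpoint. Record whether each was found at a scheduled or an unscheduled contact, and add a sensitivity comparison limited to events from the scheduled checklist. That restriction should not become the main analysis, because it would drop real events that 10.2.2 counts.
- **8.1 and 9.3:** reconcile the promised blood tests with a schedule that has no row for them.
- **6.5:** state whether the masked outcome evaluator covers adverse events.

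The cost is a short form, a field on the case report form and a few sentences. No extra visits are needed. The limits are that recall over a nominal 10 weeks is imperfect and may itself differ by arm because patients know their drug. The checklist also does not reach the 28 days after treatment, for which 9.3 shows no contact.
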